### Eligibility criteria

The study population consists of male and female patients aged 18 years and older who will undergo TME for histologically confirmed rectal cancer staged as locally advanced (cT2N0-T3N0-N+), without distant metastases or high-risk features including as MRF involvement, EMVI, pathologic lateral pelvic lymph nodes (LPLN) or invasion of adjacent organs (cT4).

#### Inclusion criteria.

Pathologically confirmed rectal cancerRectal cancer within 6–12 cm from anal verge confirmed by sigmoidoscopy or located between the anorectal junction and peritoneal reflection identified by MRIClinically staged with pelvic MRI and thoracoabdominal computed tomography (CT)Local clinical stages cT2N+, cT3N0 and cT3N+Patients without MRF involvement assessed by MRI (≤1 mm)Patients without pathological LPLN (short axis ≥7 mm) on MRIPatients without EMVI on MRIPatients who underwent open, laparoscopic or robotic TME

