This trial aims to investigate whether avoiding nCRT provides oncological outcomes equivalent to the standard approach in patients with locally advanced mid-rectal cancer who have a low risk of local recurrence. By leveraging MRI-based risk stratification and a real-world, multi-center cohort, this study seeks to refine patient selection criteria for nCRT and reduce unnecessary exposure to chemoradiotherapy in low-risk patients.

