### Main question

H_0_: There is no difference in 3-year disease-free survival between direct TME and TME following nCRT in patients with mid-rectal cancer (cT2N+ and cT3Nx) without high-risk MRI findings regarding local recurrence.

H_1_: Direct TME is associated with worse 3-year disease-free survival compared to TME following nCRT In patients with mid-rectal cancer (cT2N+ and cT3Nx) without without high-risk MRI findings regarding local recurrence.

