#### Exclusion criteria.

cT4 tumors assessed by MRIStage IV disease assessed by MRI and/or CTPatients with MSI (+) in TME pathologyPatients who received neoadjuvant immunotherapyEmergency surgeryClinical obstructionPrevious pelvic radiotherapyPatients treated without a multidisciplinary council decisionInflammatory bowel diseases (Crohn’s disease, Ulcerative colitis)Familial adenomatous polyposis (FAP), attenuated FAP, and other polyposis syndromesHereditary non-polyposis colorectal cancer (Lynch syndrome)Synchronous colon tumors

Patients undergoing surgeries other than TME (e.g., partial mesorectal excision, rectosigmoid resection, end colostomy) will not be included in the study. Following data entry, patients for whom pathology reports indicate that TME was not performed or who has missing data regarding inclusion criteria will be excluded from the study. Patients who are unable to complete neoadjuvant therapy for any reason (such as toxicity, non-compliance, or accessibility issues) will not be excluded from the study. These patients will be evaluated within the neoadjuvant therapy group. Accordingly, when analyzing this aspect, an intention-to-treat analysis will be conducted without cross-over.

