### Statistical methods

During the study, missing data analyses and data quality assessments will be actively conducted, and measures to prevent data loss and enhance data quality will be implemented as appropriate. All statistical analyses will be conducted by experts from the TSCRS Biostatistics and Bioinformatics Analysis Unit using SPSS (SPSS Inc, Chicago, IL) software packages.

Multivariable regression analyses will be conducted to evaluate the effect of treatment strategy (direct TME vs. nCRT followed by TME) on the primary and secondary outcomes. The following covariates will be included in the models based on clinical relevance and literature review: age, sex, clinical T stage (cT2 vs. cT3), clinical N stage (N0 vs. N+), tumor differentiation, regimens of neoadjuvant treatment (long-course CRT, short-course RT, TNT with long or short-course RT), interval between neoadjuvant RT/CT and surgery, comorbidities (e.g., Charlson Comorbidity Index), performance status, postoperative complications (Clavien-Dindo), tumor histology, pathologic TME quality (pathologic completeness of the mesorectum), and center effect (as a random effect if appropriate).

For time-to-event outcomes such as disease-free survival (DFS) and overall survival (OS), Cox proportional hazards regression models will be used to estimate hazard ratios and 95% confidence intervals. The proportional hazards assumption will be tested using Schoenfeld residuals.

To address potential selection bias due to the non-randomized design, propensity score methods will be applied. Specifically, propensity scores for receipt of nCRT (vs. direct TME) will be estimated using logistic regression including the aforementioned covariates. The primary analysis will adjust for the propensity score as a covariate in the Cox model. Sensitivity analyses will be conducted using propensity score matching (1:1 nearest neighbor matching without replacement) and inverse probability of treatment weighting (IPTW) to ensure the robustness of results.

Patients lacking the main data specified in the inclusion and exclusion criteria, demographic data, or follow-up data related to the primary endpoint will be completely excluded from the study. Patients with missing data from other variables or secondary endpoints will only be excluded from those specific analyses, and secondary endpoints will be evaluated using data from patients with complete datasets.

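### The tumour-location criterion lets tumours below the 6 cm limit enter by MRI in a study of mid-rectal cancer, and tumour height is not among the listed adjustment covariates

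*Protocol article*

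**What the plan says.** **Location.** Under Inclusion criteria, the tumour must be "within 6–12 cm from anal verge confirmed by sigmoidoscopy or located between the anorectal junction and peritoneal reflection identified by" MRI. The word joining the two descriptions is *or*, so meeting either one is enough. No rule says which prevails when they disagree.

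**Population.** The Introduction states the aim for "patients with locally advanced mid-rectal cancer who have a low risk of local recurrence". The null hypothesis under Main question compares direct TME with "TME following nCRT in patients with mid-rectal cancer (cT2N+ and cT3Nx) without high-risk MRI findings", and the alternative is worded for the same segment: "Direct TME is associated with worse 3-year disease-free survival compared to TME following nCRT In patients with mid-rectal cancer". The Abstract and the sample-size paragraph also speak of mid-rectal tumours.

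**Exclusions.** None concerns tumour height. The nearest is on the operation: "Patients undergoing surgeries other than TME (e.g., partial mesorectal excision, rectosigmoid resection, end colostomy) will not be included in the study".

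**Adjustment.** The covariate list under Statistical methods opens with "age, sex, clinical T stage (cT2 vs. cT3), clinical N stage (N0 vs. N+), tumor differentiation, regimens of neoadjuvant treatment". After the interval to surgery, comorbidities and performance status, it closes with "postoperative complications (Clavien-Dindo), tumor histology, pathologic TME quality (pathologic completeness of the mesorectum), and center effect". The propensity score is built from the same list. The primary analysis enters that score in a Cox model; matching and inverse probability weighting are sensitivity analyses.

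**The concern.** There are two linked problems.

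The first is the population. The two location routes are not equivalent. The sigmoidoscopy route has a lower limit of 6 cm. The MRI route has the anorectal junction, which is where the rectum begins. A patient who fails the first can use the second, so the enrolled cohort may be wider than the one the hypotheses name.

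The second is confounding. Clinicians choose the treatment. Height plausibly affects both that choice and the outcomes: recurrence, the level of the anastomosis and bowel function. If low tumours go more often to nCRT and do worse, direct TME looks better on DFS and local recurrence, and nCRT looks worse on LARS. The Discussion describes the aim as showing non-inferiority of upfront TME, so a bias in that direction would be the unsafe one. All three propensity-score analyses share the omission, so agreement among them would not reveal it.

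**Working it through.** **Step 1. The two routes side by side.**

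| | Sigmoidoscopy route | MRI route |
|---|---|---|
| Lower limit | 6 cm from anal verge | anorectal junction, no distance given |
| Upper limit | 12 cm from anal verge | peritoneal reflection, no distance given |
| Sufficient alone? | yes | yes |

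A tumour above the anorectal junction but less than 6 cm from the verge fails the first route and meets the second. It is eligible on location.

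**Step 2. Does anything else remove it?** The exclusion of operations other than TME may remove some very low tumours. A low tumour treated by TME stays in. The Interventions section calls both strategies guideline-concordant for mid-rectal tumours specifically, so that argument for comparability does not extend to the extra patients.

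**Step 3. Is height adjusted for?** Reading the covariate list to its end, neither height, nor distance from the verge, nor location appears. Stage, differentiation and histology do not measure height. Complications and TME quality arise after treatment and cannot stand in for a baseline feature. A centre effect does not correct height differences between patients within one centre.

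**Step 4. The plan's own figure, for scale.** The sample-size paragraph gives 80% DFS in both groups, α = 0.05, 80% power and 396 patients. It states neither a margin nor the sidedness. A 10-point margin with a one-sided 5% test reproduces the total:

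n per group = (1.645 + 0.842)² × (0.8×0.2 + 0.8×0.2) / 0.10² = 6.18 × 0.32 / 0.01 ≈ 198, so 2 × 198 = 396.

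The figure does not depend on the location rule. It gives a standard error for the difference of √(0.32/198) = 0.040, or 4.0 points.

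**Step 5. Illustrative size.** Bias = (difference between groups in the share of low tumours) × (outcome gap between low and mid tumours). Neither input is in the documents. The assumed ranges are:

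| Share difference | DFS gap 5 points | DFS gap 10 points |
|---|---|---|
| 10 points | 0.5 | 1.0 |
| 30 points | 1.5 | 3.0 |

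For LARS, assume that major LARS is 20–30 points more frequent after low resection. The same share differences then give 0.10 × 20 = 2 to 0.30 × 30 = 9 points.

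**Step 6. What that would do at the inferred margin.** One-sided error = Φ(bias/0.040 − 1.645). With no bias this is 5%. At 0.5 points it is about 6.4%, and at 3.0 points about 18.4%. These figures take an unadjusted comparison of proportions and a margin and sidedness that are inferred. They show scale only.

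**The case against.** The strongest reply is that the consequence cannot be measured. The documents give no distance for the anorectal junction or the peritoneal reflection, so the number of low tumours admitted cannot be computed. The text says mid-rectal throughout, so the MRI wording may be a loose landmark for the same segment. The Introduction cites a guideline group lying above the levator muscles, which may be its origin. This stands as to size. It does not remove the problem, because a site applying the criterion as written may enroll below 6 cm.

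The eligibility rules also remove mesorectal fascia involvement, EMVI, pathological lateral nodes and cT4 disease. Any prognostic gap between low and mid tumours is then likely to be narrower than in unselected patients. This stands, and is a reason not to lean on the upper end of the illustrative range.

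The covariate list may not be closed. The Restaging section allows further variables in the regression models, an analysis plan may exist, and Limitations concedes residual confounding in general terms. This stands in part. But the article commits to the listed covariates and builds the propensity score from them, without height.

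A reader might also infer that tumours at 11–12 cm lying above the peritoneal reflection contaminate the cohort from the other end. The documents do not support that. Such tumours lie within the 6–12 cm range, which is the route that fits the mid-rectal description, and partial mesorectal excision and rectosigmoid resection are excluded.

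**Conclusion.** The point holds on the text. The location criterion is wider at its lower end than the mid-rectal population of the hypotheses, and the listed covariates would leave an imbalance in tumour height unadjusted in the primary and both sensitivity analyses. The first part rests only on the anorectal junction being the lower end of the rectum.

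It is tempting to go further and say that the comparison is biased towards omitting nCRT by a known amount. The documents do not support this. They give no data on treatment choice by height, on the share of low tumours or on their outcomes. The direction is plausible, and 0.5–3 DFS points follows only from the assumed inputs. Even the top of that range is under a third of the 10% difference that the protocol treats as unacceptable, and that figure is a stopping criterion, not a stated margin.

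This should be fixed before recruitment, but it does not by itself invalidate the study.

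**What to change.** 1. Reconcile the location criterion with the mid-rectal population named under Main question, so that one route cannot bypass the limits of the other. Two examples are a single definition of mid-rectum applied to every patient, or a requirement that both descriptions are met. The investigators must choose the definition and use it consistently in the aim, hypotheses and eligibility text.
2. Record baseline distance from the anal verge for every patient. Add it as a continuous covariate to the propensity score and to the DFS, local recurrence and LARS models.

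Both parts are needed. Adjustment does not make a wider cohort mid-rectal, and height still varies within 6–12 cm.

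The cost is one amended inclusion line and one more covariate. Some patients who qualify only by the MRI route become ineligible; if both descriptions are required, so do those who qualify only by sigmoidoscopy. How many cannot be told from the documents. The article states that recruitment had not begun, so the change can be made before any patient is affected.

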#### Exclusion criteria.

cT4 tumors assessed by MRIStage IV disease assessed by MRI and/or CTPatients with MSI (+) in TME pathologyPatients who received neoadjuvant immunotherapyEmergency surgeryClinical obstructionPrevious pelvic radiotherapyPatients treated without a multidisciplinary council decisionInflammatory bowel diseases (Crohn’s disease, Ulcerative colitis)Familial adenomatous polyposis (FAP), attenuated FAP, and other polyposis syndromesHereditary non-polyposis colorectal cancer (Lynch syndrome)Synchronous colon tumors

Patients undergoing surgeries other than TME (e.g., partial mesorectal excision, rectosigmoid resection, end colostomy) will not be included in the study. Following data entry, patients for whom pathology reports indicate that TME was not performed or who has missing data regarding inclusion criteria will be excluded from the study. Patients who are unable to complete neoadjuvant therapy for any reason (such as toxicity, non-compliance, or accessibility issues) will not be excluded from the study. These patients will be evaluated within the neoadjuvant therapy group. Accordingly, when analyzing this aspect, an intention-to-treat analysis will be conducted without cross-over.

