### Trial registration and ethical considerations

The study protocol has been prepared in accordance with SPIRIT guidelines (S1 File) and approved by Baskent University Ethical Review Board on 15-06-2025 (Approval number: KA24/461). The trial protocol has been registered before starting inclusion (NCT06823297, ClinicalTrials.gov). The study has not started patient recruitment yet and the anticipated recruitment date is 01.08.2025. The anticipated timeline is as follows: Primary recruitment completion: August, 2030, study completion: August, 2030.

Written informed consent for inclusion in the study will be obtained from all eligible patients prior to any treatment (neoadjuvant treatments or surgery), in conjunction with the treatment consents. A distinct informed consent form for the study, prepared by the steering committee and approved by the ethics committee, exists separately from the institutional informed consent form. The attending surgeon is responsible for providing the patient with comprehensive information regarding the study and securing this consent in written form. Another healthcare provider (nurse, resident, surgeon) will witness the consenting process.

In this study, participant data and biological specimens are not being collected for ancillary studies. However, each institution participating in the study may include statements in their own surgical informed consent forms regarding the use of patient information and specimens in other studies. This responsibility lies with the respective institution and the surgeon.

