### Trial design

The CANO trial is a prospective, non-randomized, observational, cohort study. Patients undergoing TME will be included in the study, with a comparative analysis between those receiving neoadjuvant chemoradiotherapy and those who do not. The design precludes any possibility of cross-over between the groups.

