### Interventions

The standard of care for the treatment of locally advanced rectal cancer is TME. In patients with cT2N+, cT3N0, and cT3N+ mid-rectal tumors, the administration of nCRT, as well as the direct TME, are both considered guideline-concordant standard treatment approaches and are widely practiced [11,12]. In this study, data from patients undergoing TME as part of routine medical care will be collected prospectively. No additional interventions, treatments and follow-up protocols outside of standard care will be implemented. At the end of the study, patients will be categorized into two groups based on whether they received nCRT and the two groups will be compared in terms of primary and secondary endpoints. No treatment or monitoring protocols differing from routine practice will be proposed for patients or surgeons in the study. The natural prognosis of the treatment arms will be observed.

All the patients undergoing TME described as a precise dissection of the rectum along with the surrounding mesorectal tissue and all pararectal lymph nodes are eligible for the study [13].

**Direct TME Group:** Patients who undergo direct TME without neoadjuvant treatment.

**nCRT Group:** Patients who receive nCRT prior to TME.

Neoadjuvan CRT treatments include all conventional chemoradiotherapy regimens or total neoadjuvant chemoradiotherapy regimens (standard short or long course radiation and/or any standard chemotherapy regimen) described in European and American guidelines [11,12]. The details of radiotherapy and chemotherapy treatments will be recorded, including dosage, frequency, duration, complications, completion status, and the waiting period between treatments. Routine follow-up information for all patients including morbidity, radiologic assessments, recurrence, mortality be recorded in the database for the first five years post-surgery. Patient-reported quality of life scales will be recorded at baseline (prior to the initiation of treatment) and subsequently at 1, 3, and 5 years.

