### Sample size and recruitment

The literature reports a mean 3-year disease-free survival rate of 75–85% for the sample to be included in the study [16]. For patients with mid-rectal tumors (cT2N+ and cT3N0) without high risk MRI findings, the 3-year disease-free survival rate was estimated to be 80% for both direct TME and TME following neoadjuvant chemoradiotherapy. Under these conditions, with α = 0.05 (95% confidence interval) and 80% power, the power analysis indicated that a total of 396 patients (1:1 ratio) would be required. Considering a 10% dropout rate, it is planned to include 218 patients in each group, for a total of 436 patients.

According to data from the Turkish Ministry of Health, General Directorate of Public Health, a total of 24,312 patients were diagnosed with rectal cancer between 2020 and 2024, of whom 17,896 underwent surgery (https://hsgm.saglik.gov.tr/tr/kanser.html). Since this study will be conducted nationally under the sponsorship of the main society of Turkish colorectal surgeons TSCRS, we anticipate reaching the targeted patient number within five years from the start of the study. To achieve this goal, TSCRS will utilize various channels, including mailing, social media, and its website, to announce the study and inform surgeons about the protocol.

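### The exclusion text lists end colostomy among surgeries other than TME and leaves open whether a TME without anastomosis is eligible

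*Protocol article*

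**What the plan says.** Four sections of the protocol article bear on whether a TME that ends in a stoma belongs in the cohort.

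- **Exclusion criteria:** "Patients undergoing surgeries other than TME (e.g., partial mesorectal excision, rectosigmoid resection, end colostomy) will not be included in the study". A later check follows in the same paragraph: "Following data entry, patients for whom pathology reports indicate that TME was not performed or who has missing data regarding inclusion criteria will be excluded".
- **Interventions:** "All the patients undergoing TME described as a precise dissection of the rectum along with the surrounding mesorectal tissue". The sentence goes on to name the nodes beside the rectum and counts every such patient as eligible. The definition concerns what is removed. It says nothing about how the bowel is left.
- **Inclusion criteria:** the criterion on surgery asks for a TME and names the permitted approaches. It does not mention reconstruction.
- **Trial registration and ethical considerations:** "Written informed consent for inclusion in the study will be obtained from all eligible patients prior to any treatment (neoadjuvant treatments or surgery"). Consent therefore precedes the operation that decides the surgical exclusion.

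The Exclusion criteria section also promises that "an intention-to-treat analysis will be conducted without cross-over". That promise is attached to patients who do not complete neoadjuvant therapy, not to patients removed because of the operation they received.

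**The concern.** An end colostomy describes how the bowel is left after surgery. TME, as the Interventions section defines it, describes what was dissected. The two can occur in the same operation, so listing one as an example of not being the other leaves a group of patients without a clear status: those with a complete TME and no anastomosis.

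On the wording of the exclusion they are out. On the wording of the Interventions section they are in. Each centre's own team enters its data, so centres could apply the rule differently.

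If they are out, the cohort is selected on something that happens after consent and, in one group, after nCRT. The regression and propensity-score models in Statistical methods work on the patients who remain and cannot restore those removed. If the removed patients differ between groups in number or prognosis, the 3-year DFS contrast among the rest is not the contrast among all patients who had a TME.

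**Working it through.** **Step 1. The sections side by side, for a patient with a complete TME and an end colostomy**

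| Section | Test applied | Result |
|---|---|---|
| Inclusion criteria | TME by a permitted approach | Eligible |
| Interventions | Dissection meets the TME definition | Eligible |
| Exclusion criteria, check after data entry | Does pathology show that TME was not done? | Not removed |
| Exclusion criteria, list of examples | End colostomy named as other than TME | Excluded on its face |

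Three tests keep the patient and one, read literally, removes the patient.

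**Step 2. Does the context settle the meaning?** Not fully. The other two examples (partial mesorectal excision and rectosigmoid resection) are resections, which suggests that end colostomy is also meant as a type of resection. The same section already excludes emergency surgery, clinical obstruction, stage IV disease and cT4 tumours, so a stoma without resection is left with little to cover. Against that, the three terms illustrate surgeries other than TME, so the phrase can be read as an end colostomy without TME.

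**Step 3. When would exclusion bias DFS?** The plan has no figure on this point, so what follows is purely illustrative. One input is the plan's: "the 3-year disease-free survival rate was estimated to be 80% for both direct TME and TME following neoadjuvant chemoradiotherapy". Two are assumptions: the share *f* of a group excluded for end colostomy, and the 3-year DFS *d* in those patients, taken as 50% to 70%. With true DFS of 80% in the whole group, the DFS among retained patients is

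(0.80 − *f* × *d*) / (1 − *f*).

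- Equal *f* and equal *d* in both groups: the retained values are the same, and the bias is 0.
- *f* = 5% for direct TME and 15% for nCRT, *d* = 70%: 0.765/0.95 = 0.8053 and 0.695/0.85 = 0.8176, a spurious difference of 1.2 points.
- The same shares, *d* = 60%: 0.770/0.95 = 0.8105 and 0.710/0.85 = 0.8353, or 2.5 points.
- The same shares, *d* = 50%: 0.775/0.95 = 0.8158 and 0.725/0.85 = 0.8529, or 3.7 points.
- Shares of 5% and 10%, *d* from 70% to 50%: 0.6 to 1.8 points.
- Equal shares of 10%, but *d* = 60% in one group and 70% in the other: 0.740/0.90 = 0.8222 and 0.730/0.90 = 0.8111, or 1.1 points.

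Where the shares are unequal, these examples work against direct TME. The sign reverses if direct TME has the larger share.

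**Step 4. Why no power figure is given.** The planned total of 396 can be matched as a non-inferiority calculation: 2 × 0.80 × 0.20 × (1.645 + 0.842)² / 0.10² = 197.9, so 198 per group. That needs a 10-point margin and a one-sided 5% level, neither of which Sample size and recruitment states. The planned analysis is also a propensity-adjusted Cox model, not a comparison of two raw proportions. A power loss would add further assumptions to assumed rates.

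**The case against.** The strongest reply is that nothing conflicts. The rule bars surgeries other than TME, and the parenthesis only gives examples. Read that way, end colostomy means a stoma without a TME, which is rightly excluded. A full TME with a stoma passes the pathology check and the Inclusion criteria and fits the Interventions definition. No section asks for an anastomosis.

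This reading is possible, and it is why the point cannot be put as a certain error. It does not remove the point, because the text does not say so and the neighbouring examples lean the other way.

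A reader might also infer several stronger things that the documents do not support:

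- **That nCRT changes how often an end colostomy is made.** The documents do not say so and give no rate for either group.
- **That the Trial design section repeats the definition.** It says only that "Patients undergoing TME will be included in the study", without defining the operation.
- **That a quality-of-life outcome on permanent stoma would be lost.** No stoma outcome is listed. The quality-of-life endpoints are two questionnaires, both secondary.
- **That stoma type is not recorded.** The data section says that surgical variables and type of surgery are collected, and the variable list is in a supplement that is not shown.

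**Conclusion.** The point holds as an unresolved conflict in the eligibility wording. Whether a TME without anastomosis is in or out cannot be decided from the protocol article. If it is out, consented patients leave the cohort because of an operative result decided after any nCRT, and the intention-to-treat statement does not cover them.

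The consequence for 3-year DFS is conditional. There is no bias if the exclusions are alike in both groups in share and prognosis. Under the assumed unequal rates above it is roughly 1 to 4 points, in either direction. Those values show the order of magnitude under assumption and are not an estimate for this trial. A claim that the primary comparison is biased, or that power falls by a given amount, would go beyond the documents. No change to the sample size follows.

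**What to change.** 1. Reconcile the Inclusion criteria, the Exclusion criteria and the Interventions section. Either delete end colostomy from the examples or replace it with end colostomy without TME. Eligibility then depends only on whether the resection meets the definition in Interventions.
2. State that patients with a TME and an end colostomy stay in the DFS, overall survival and local recurrence analyses, and that the LARS score is analysed only where continuity is restored.
3. Report, by treatment group and with reasons, the patients who consented and were then excluded because of the operation performed.

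The cost is one phrase in the eligibility text, a sentence on the analysis set and one line in the patient flow report. No extra procedure or visit is needed. The article says that recruitment has not begun, so the wording can be settled before any centre has to apply it.

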### Outcomes

#### Primary outcome measure.

3-year DFS: The proportion of patients who remain free of disease recurrence (local or distant) three years after surgical intervention. DFS will be assessed through clinical evaluations, imaging studies, and pathology reports at regular follow-up intervals.

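### Analysing only patients who reach TME, grouped by nCRT received and timed from surgery, removes pre-surgical failures and non-surgical responders mainly from the nCRT arm

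*Protocol article*

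**What the plan says.** All references are to the Protocol article.

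- **Enrolment.** Under Trial registration and ethical considerations: "Written informed consent for inclusion in the study will be obtained from all eligible patients prior to any treatment".
- **Population.** Trial design states: "Patients undergoing TME will be included in the study, with a comparative analysis between those receiving neoadjuvant chemoradiotherapy and those who do not". The Inclusion criteria list having undergone open, laparoscopic or robotic TME. The Exclusion criteria add: "Patients undergoing surgeries other than TME (e.g., partial mesorectal excision, rectosigmoid resection, end colostomy) will not be included in the study". They also remove at a later stage those described as "Following data entry, patients for whom pathology reports indicate that TME was not performed".
- **Groups.** Under Interventions: "At the end of the study, patients will be categorized into two groups based on whether they received nCRT". The nCRT group is defined there as patients who receive nCRT before TME.
- **Time origin.** The Primary outcome measure is the proportion free of local or distant recurrence "three years after surgical intervention".
- **Intention-to-treat.** The Exclusion criteria say: "Patients who are unable to complete neoadjuvant therapy for any reason (such as toxicity, non-compliance, or accessibility issues) will not be excluded from the study". They stay in the neoadjuvant group, and the text concludes: "Accordingly, when analyzing this aspect, an intention-to-treat analysis will be conducted without cross-over".

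**The concern.** The question is about two strategies chosen before treatment: go straight to TME, or give nCRT first. A fair comparison follows everyone from that choice. Here, membership of the cohort depends on a later event, reaching TME, and the two strategies reach it after very different delays. Direct-TME patients go to surgery without a treatment period in between. nCRT patients first pass through chemoradiotherapy or total neoadjuvant therapy, a waiting interval and restaging. The Restaging section itself expects CT at that point to look for distant metastases.

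A patient who progresses, dies or becomes unresectable in that period, or who is managed without surgery after a good response, never enters the nCRT arm as analysed. Losing failures flatters nCRT. Losing good responders penalises it. The propensity methods in Statistical methods balance measured characteristics among included patients and cannot bring back those who were removed. The Limitations section acknowledges selection bias from non-randomisation but not this loss after enrolment. At stake is whether the DFS difference describes the strategies or only those patients who got through to surgery.

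**Working it through.** **1. The passages side by side.** Consent before treatment means that patients are known to the study before nCRT starts. The general eligibility paragraph speaks of patients who will undergo TME, which could mean planned surgery. The Inclusion and Exclusion criteria settle it: whoever does not have TME is out. The intention-to-treat sentence keeps patients with incomplete nCRT, but they must still pass the TME requirement. No passage keeps an nCRT patient who never reaches TME.

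**2. Inputs.** From Sample size and recruitment: 80% 3-year DFS in both groups, α 0.05 (sidedness not stated), 80% power, 396 patients, 436 with 10% dropout. No margin is stated. The Discussion speaks of non-inferiority, and the only 10% difference is in the discontinuation criteria.

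**3. Reproducing the plan's figure.** With a 10-point margin and one-sided α 0.05:

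n per arm = (1.6449 + 0.8416)² × (0.80×0.20 + 0.80×0.20) / 0.10² = 6.183 × 0.32 / 0.01 = 197.9, so 198 per arm and 396 in total. Then 198 × 1.10 = 217.8, so 218 per arm and 436 in total.

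One-sided 0.025 would give 252 per arm, which does not match. Two superiority contrasts come close (80% v 90% two-sided, 398; 80% v 69% one-sided, 388), but neither fits 80% in both groups. The 10-point margin is therefore an inference. It serves here only as a yardstick.

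**4. Effect of the selection.** Assume true 3-year DFS of 80% among all nCRT starters. Let f be the share who never reach TME and q their DFS. The documents give neither. Observed nCRT DFS = (0.80 − f×q)/(1 − f).

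| f | q | Working | Observed | Shift (points) |
|---|---|---|---|---|
| 5% | 0 | 0.800/0.95 | 84.2% | +4.2 |
| 5% | 0.3 | 0.785/0.95 | 82.6% | +2.6 |
| 5% | 0.9 | 0.755/0.95 | 79.5% | −0.5 |
| 10% | 0 | 0.800/0.90 | 88.9% | +8.9 |
| 10% | 0.3 | 0.770/0.90 | 85.6% | +5.6 |
| 10% | 0.9 | 0.710/0.90 | 78.9% | −1.1 |

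The shift is zero at q = 0.80, and q = 0 is the upper bound for each f. Losses of both kinds partly cancel: 2% failures (q = 0) plus 10% responders (q = 0.9) give (0.80 − 0.09)/0.88 = 80.7%.

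**5. Consequence for the conclusion.** Use 198 per arm, margin 0.10, one-sided 0.05, an unadjusted difference in proportions and no selection in the direct arm. With p_C the observed nCRT DFS and p_T the direct-TME DFS, the probability of declaring non-inferiority is Φ((0.10 − (p_C − p_T))/SE − 1.645), where SE = √[(p_C(1−p_C) + p_T(1−p_T))/198].

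- Direct TME truly 80%: 80.0% power without selection, 59.4% at f = 5%, q = 0.3, and about 44% at f = 5%, q = 0.
- Direct TME truly 70%, at the inferred margin: false-positive rate 5% without selection, 6.4% at f = 5%, q = 0.9, and 8.2% at f = 10%, q = 0.9.

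**6. How many early events are plausible.** A constant hazard matching 80% at 36 months is −ln(0.80)/36 = 0.0062 per month. Over an assumed 3 to 8 months before surgery, 1 − exp(−0.0062×3) = 1.8% and 1 − exp(−0.0062×8) = 4.8%. Both the window and the constant hazard are assumptions. These are largely the same early failures as in step 4, not an additional bias.

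**The case against.** Several stronger readings are tempting, and the documents do not support them.

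- **That intention-to-treat is claimed for the whole comparison.** The sentence is limited to incomplete nCRT, and on that narrow point the protocol follows it. Elsewhere the TME-only comparison is stated openly.
- **That planned-nCRT patients who never start are moved to direct TME.** Grouping by nCRT received points that way. But the Exclusion criteria keep patients unable to complete for any reason, accessibility included, in the nCRT group. The text is unclear rather than settled.
- **That this is immortal time.** Both clocks start at surgery, so no pre-surgical time is credited to either arm. The problem is selection on reaching surgery, with a late time origin.
- **That only one arm is affected.** Exclusion for another operation, or for pathology showing no TME, applies to both. The loss is asymmetric, not exclusive.
- **That nCRT must look better.** A calculation that drops failures alone gives an upper bound. Losing responders works the other way.
- **That stage IV, obstruction and emergency surgery remove patients during nCRT.** They may be baseline criteria. No time point is given.

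It is also fair that nCRT dates, completion status and waiting periods are recorded, so an analysis from treatment start among TME patients is possible. That would not recover those who never reach TME. Nor is the matter simply left to an analysis plan: population, grouping and time origin are all fixed in the article.

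**Conclusion.** The concern holds as selection on reaching surgery. The primary comparison describes patients who reached TME, not the strategies of giving or omitting nCRT, and the planned propensity methods cannot correct that. Size and sign cannot be derived from the documents. Under the assumptions shown, a 5% loss moves observed nCRT DFS to between 79.5% and 84.2%, and a 10% loss of patients with 90% DFS moves it to 78.9%. Against the inferred 10-point margin, the upward shifts can hide true non-inferiority and the downward shifts can falsely support it. The figures rest on assumed f and q, on transferring the planning value of 80% (stated for TME with or without nCRT) to all nCRT starters, and on an unadjusted comparison of proportions. The sample size is not what fails here.

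**What to change.** 1. Define the cohort at consent or the multidisciplinary decision, assign the group by the plan recorded there, and start DFS and OS at that date.
2. Keep all consented patients who are eligible at baseline, whether or not TME follows. This also settles the never-starter question; reconcile Exclusion criteria and Interventions accordingly.
3. Count progression, metastasis at restaging or death before surgery as DFS events, and state in advance how patients who never have surgery are scored. The present definition covers only recurrence after surgery.
4. State that the stage IV, obstruction and emergency-surgery exclusions apply at baseline only.
5. The MSI exclusion depends on TME pathology. For patients without a specimen, use biopsy MSI where available; otherwise keep them as MSI-unknown, with a sensitivity analysis.
6. Report the TME-only, from-surgery comparison as a sensitivity analysis.

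The change is feasible: the article reports that recruitment had not begun, consent precedes treatment, patients treated without a multidisciplinary decision are already excluded, and neoadjuvant dates are recorded. The cost is more than wording: a field for plan and decision date, an extended DFS definition, follow-up of the presumably few patients who never reach TME, some unknown MSI status, and a slightly more heterogeneous population. Data on patients dropped before TME would be hard to recover later.
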